### Monitoring: harms

The risks of harm to participants in this study are minor. However, dealing with the relative’s illness can also lead to psychological stress. If participants discontinue the intervention, the reasons (e.g., subjective adverse effects on psychological well-being) are documented. A serious adverse event (SAE) for the study is suicidality and suicide, which may or may not be causally related to the intervention or study aspects. SAEs will be documented and immediately reported to the principal investigator.

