#### Control group (CG)

Relatives of the CG receive written information about the offers (e.g., counseling, relaxation groups) of psycho-oncological care at the CCCMF by giving the patient the information flyer of the psycho-oncological department. This offer of psycho-oncological care with single and group interventions for patients and relatives corresponds to usual care. Therefore, psycho-oncological counseling is also possible in the CG but is based on personal needs and active engagement. This needs-based counseling in usual care is not structured according to the CALM approach. Furthermore, it is not standard to schedule as many counseling sessions within 6 weeks. This control condition was chosen for ethical reasons.

No specific psycho-oncological intervention is proactively offered to the lung cancer patients in both study arms. However, they can request the support of the psycho-oncological team of the CCCMF (usual care).

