#### Distress

The Distress Thermometer is a simple and sensitive screening tool to assess psychosocial stress in oncology patients [33, 34]. It assesses distress within the last week on an 11-point rating scale from 0 (not at all stressed) to 10 (extremely stressed). A cutoff value of 5 or more indicates high distress and need for support [33].

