### Recruitment

Lung cancer patients treated in the University Hospital Würzburg and their relatives are recruited either in the pneumatological outpatient clinic or by contacting the patients or their relatives by phone. Eligible persons are informed about all relevant aspects of the study, i.e., the psycho-oncological intervention for the relatives, the procedure, and assessments. It is also explained that participation in the study is voluntary and can be terminated at any time without giving a reason. In the case the patients and their relatives are interested in the study, they get written study information, a flyer with the offers of the psycho-oncological department of the CCCMF, the baseline set of questionnaires (T0), and an informed consent form (in person or delivered by mail). After written consent is provided and the initial questionnaires (T0) are completed, a psycho-oncologist will contact relatives in the IG to set a date for an initial appointment, whereas CG will not be actively contacted.

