If the CALM intervention shows positive effects on the psychosocial outcome of the relatives, the CALM intervention should be implemented in routine care. Altogether, study results will contribute to a better understanding of the effectiveness of a psycho-oncological intervention for highly impaired cancer patients and their relatives.

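### The only stated route for recording non-serious psychological harm is stopping the intervention, so the plan yields no count of people who worsen by randomised arm

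*Protocol article*

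**What the plan says.** All references are to the protocol article.

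- **Named risk.** *Monitoring: harms* calls the risks minor but adds: "However, dealing with the relative’s illness can also lead to psychological stress".
- **Non-serious harm.** The same section states one route: "If participants discontinue the intervention, the reasons (e.g., subjective adverse effects on psychological well-being) are documented".
- **Serious harm.** Suicidality and suicide count as serious adverse events and are documented and reported. This is not tied to an arm or to discontinuation.
- **Leaving.** *Recruitment* tells participants that "participation in the study is voluntary and can be terminated at any time without giving a reason".
- **Control group.** After baseline a psycho-oncologist contacts IG relatives, "whereas CG will not be actively contacted". *Control group (CG)* adds that "psycho-oncological counseling is also possible in the CG but is based on personal needs and active engagement".
- **Data in both arms.** Table 2 has GAD-7, PHQ-9 and DT at T0 and T1 for relatives and patients. *Distress* gives one threshold: "A cutoff value of 5 or more indicates high distress and need for support".
- **Analysis.** The end of *Quality of life* says that the arms are compared at T1 on mean scores. *Main research question* uses ANCOVA adjusted for baseline, two-sided. *Secondary research question* compares patients according to whether their relative had fewer than two consultations or at least two.
- **Intended use.** The *Discussion* states: "If the CALM intervention shows positive effects on the psychosocial outcome of the relatives, the CALM intervention should be implemented in routine care".

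**The concern.** A record of harm informs a randomised comparison only if an event has a similar chance of being recorded in each arm. Here recording depends on leaving a programme of sessions that only one arm is assigned. The record will therefore mainly describe IG relatives who stop and say why.

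This matters because the *Background* says that, to the authors' knowledge, the CALM manual has not been applied to relatives before. Its content includes mortality and concerns about the future. The article also links positive effects to use in routine care. A reader weighing that step would want to know how many relatives got worse under CALM and how many under usual care. The planned outputs do not give that number, although the scores needed for it are collected.

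**Working it through.** **1. Who can enter the non-serious harm record, as stated**

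| Person | Assigned sessions to stop? | Recorded if they worsen? |
|---|---|---|
| IG relative, stops and gives a reason | Yes | Yes |
| IG relative, stops without a reason | Yes | Not necessarily |
| IG relative, completes sessions | Yes, but does not stop | No |
| CG relative, takes up usual-care counseling and stops | None assigned; self-initiated | Unclear |
| CG relative, no counseling | No | No |
| Patient, either arm | No specific intervention | No |

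The route is asymmetric between arms and, within the IG, selective.

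**2. Does the mean comparison fill the gap?** In part. For relatives, a two-sided ANCOVA on GAD-7, PHQ-9 and DT would show an average worsening under CALM. It does not give a count of individuals. Suppose a share p worsens by w points and the rest improve by g points. The mean change is p·w − (1 − p)·g, which is an improvement whenever g > p·w/(1 − p). With p = 20% (assumed), that is g > 0.2w/0.8 = w/4. One relative in five could worsen by w while the arm's mean still improves, provided the others gain slightly more than a quarter of w.

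Two further features limit the means as a safety check:

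- *Statistical analysis* assigns pair-wise deletion to values missing through drop-out. Someone who worsens, leaves and returns no T1 form may drop out of the mean comparison as well.
- The one section devoted to patients groups them by the number of consultations their relative had, which is not the randomised arm.

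**3. The plan's own figures.** The harms section contains none. The sample size sets the precision available. With two-sided alpha 0.05 and power 0.80, n per group = 2 × (1.960 + 0.842)² / d².

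- d = 0.4: 2 × 7.85/0.16 = 98.1, rounded up to 99. The t-test version gives 99.08, rounded up to 100. The stated 100 per group reproduces.
- d = 0.6: 2 × 7.85/0.36 = 43.6, rounded up to 44, the stated interim size per group.

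**4. Precision of a worsening table.** The article gives no worsening rates, so these are assumptions. The half-width of the 95% CI for a risk difference is 1.96 × √[p₁(1 − p₁)/n + p₀(1 − p₀)/n].

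- 20% vs 10%, n = 100: 1.96 × √(0.16/100 + 0.09/100) = 1.96 × 0.050 = 9.8 points, so the CI is about 0.2 to 19.8.
- 20% vs 10%, n = 44: 1.96 × √(0.25/44) = 1.96 × 0.0754 = 14.8 points, so the CI is about −4.8 to 24.8.

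With equal rates in both arms the half-widths are:

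| Assumed rate in both arms | 100 per arm | 44 per arm |
|---|---|---|
| 5% | 6.0 points | 9.1 points |
| 10% | 8.3 points | 12.5 points |
| 20% | 11.1 points | 16.7 points |

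Power for 20% vs 10% is about 0.51 with 100 per arm and 0.26 with 44. With 100 per arm it reaches 0.80 only for a gap such as 25% vs 10%. All these figures assume complete T1 data.

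**5. Is the DT cutoff enough by itself?** No. A move from below 5 to 5 or more cannot register worsening in anyone already at 5 or more at T0, yet it counts a one-point move from 4 to 5. Its proper denominator is those below 5 at T0, which is smaller than the arm, so precision is lower than in step 4.

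**The case against.** The strongest reply is that the trial's outcomes are themselves the harm measures. Anxiety, depression and distress are collected in both arms at both times and compared two-sided. A reader might infer from the harms section that psychological harm cannot be compared between arms at all. The article does not support that: an average worsening among relatives would be visible. What remains missing is the number of individuals who worsen.

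A reader might also infer that the CG count is zero by construction, or that such an event cannot arise there. That is too absolute. CG relatives can take up usual-care counseling and stop it, Table 1 lists usual care under interventions, and the harms sentence speaks of participants rather than IG relatives. The supportable statement is that the route has no structured counterpart in the CG.

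The article is condensed. The harms section does not say that nothing else is recorded, and fuller procedures or table definitions may sit in the full protocol or analysis plan. This stands as a caveat. The point therefore rests on the rule the article states, not on detail it leaves out.

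The right to leave without a reason is a standard assurance and does not contradict documenting reasons that are given. It shows only that the record may be incomplete.

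For patients, *Outcomes and measurements* lists depression and distress among the secondary outcomes, so a comparison by randomised arm is not excluded. It is not what the section on patients specifies.

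Finally, the abstract says only that CALM may be implemented if it helps, which is softer than the *Discussion*.

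**Conclusion.** The point holds in a limited form. Followed as written, the plan gives an asymmetric and selective record of non-serious psychological harm, and no count by randomised arm of relatives or patients who worsen. The planned mean comparison covers average worsening in relatives but not individual deterioration.

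Serious events are outside this point, because their recording does not depend on arm or discontinuation. The primary analysis and the sample size are also untouched.

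The number of worsened cases that the discontinuation route would miss cannot be derived from the article, because it depends on rates that are not given. What can be sized is the precision of the remedy: for an assumed 20% vs 10%, about ±10 points at 100 per arm and ±15 at 44, with complete T1 data. That supports a descriptive table, not a test of harm. This is a cheap improvement to the plan, not a flaw in its main inference.

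**What to change.** Add to *Monitoring: harms* a descriptive table by randomised arm, separately for relatives and for patients:

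- The number and proportion who worsen from T0 to T1 on GAD-7, PHQ-9 and DT, each by a margin fixed before the interim look, with the risk difference and 95% CI. Fixing the margins early matters because the article says the analysts are not blinded.
- As a supplement only, the number moving from DT below 5 to 5 or more, with those below 5 at T0 as denominator.
- The number with missing T1 in each arm, shown alongside.
- Reasons for discontinuation, kept as a description of the IG.

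The cost is a short protocol addition and one table, with no new data collection. The downsides are that margins for three scales must be chosen and justified in advance (the article supplies only the DT cutoff), and that precision is limited, especially if the trial closes at the interim look. The table should be labelled descriptive.

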### Intervention

#### Intervention group (IG)

The intervention condition is a structured psycho-oncological intervention based on the Managing Cancer And Living Meaningfully (CALM) manual. CALM is an individualized, evidence-based psychotherapeutic intervention that focuses on four domains relevant to the challenges typically experienced by cancer patients:Symptom management and communication with healthcare providersChanges in self and relations with close othersSpiritual well-being and a sense of purposeConcerns related to the future and mortality [28]

The topics covered in the CALM domains are also relevant for relatives. Adaptations of the intervention therefore refer to the fact that in all domains, the well-being (e.g., physical and psychological symptoms) and the self-perception of the relative (e.g., change in values since the relative’s illness) are explored instead of the well-being and perception of the patient.

The CALM domains should be addressed in a tailored, individualized manner that allows for variation in time spent on each domain and the number of sessions based on the participants’ needs. Therefore, each relative receives three to six counseling sessions, each lasting 45 min. A CALM-trained psychologist delivers the sessions within 6 weeks. Three psychologists of the CCCMF (experienced psycho-oncologists/psychotherapists) were trained to do the CALM intervention at the psycho-oncological department.

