#### Quality of life

The Caregiver Quality of Life Index-Cancer (CQOLC) is used to assess the quality of life of the relatives of cancer patients. The CQOLC is a valid and reliable questionnaire that measures cancer’s psychosocial effects on relatives using 35 items. Several statements regarding how they have felt in the last few days must be rated on a 5-point Likert scale (0 = not at all; 1 = a little; 2 = somewhat; 3 = quite; 4 = very much) [38]. A higher total score (range 0–140) indicates a better health-related quality of life.

For the primary and secondary outcomes, differences between the IG and CG at T1 will be assessed using aggregated questionnaire scores (mean values).

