#### Blinding

Blinding of participants and psycho-oncologists is not possible due to the active counseling intervention. However, psycho-oncologists are not involved in recruitment and data collection. Other care providers are blind to study participation and/or assignment. For organizational reasons, the analysts will not be blinded. The members of the study team will each take on several tasks. They are responsible for enrollment, data collection, management, and statistical analysis.

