### Data collection, data management, confidentiality, and retention

Data will be assessed with patient questionnaires (paper–pencil), and medical data will be extracted from the medical record. The baseline set of questionnaires (T0) will be administered in person or delivered by mail. The follow-up questionnaires (T1) will be sent by mail with a prepaid envelope for return. Researchers will check the responses and, if necessary, contact nonresponders via telephone to promote complete follow-up.

All data will be transferred manually to a statistical program and stored on secured servers with regular backup. Double data entry will be processed for 20% of the questionnaires to assess data quality. Furthermore, range checks for data values will be performed. Questionnaires will be stored in locked cabinets. Only the research team will have access to questionnaires and data.

The data are pseudonymized to ensure confidentiality. For this purpose, each study participant is assigned a research code. The code list (including name, date of birth, SAP research number, and contact data) is accessible only to the research member responsible for the assignment and data collection. It is stored locked on an external data carrier that is not accessible to the public or other team members.

The principal investigator will retain all collected data for at least 10 years. The code list will be destroyed at the end of the study.

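### Suicidality and suicide are the only named SAE, but only IG relatives have scheduled contact through which they can surface, so relatives' SAE counts cannot be compared between arms without confounding by surveillance

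*Protocol article*

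**What the plan says.** **SAE rule.** The protocol article, Monitoring: harms, names one kind of SAE: "A serious adverse event (SAE) for the study is suicidality and suicide". It counts whether or not it is caused by the intervention or the study, and the text limits it neither to one arm nor to one member of the dyad. Handling: "SAEs will be documented and immediately reported to the principal investigator". The section does not say how a case comes to notice. It gives one other harms route: "If participants discontinue the intervention, the reasons (e.g., subjective adverse effects on psychological well-being) are documented".

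**Contact.** Under Intervention group (IG), "each relative receives three to six counseling sessions, each lasting 45 min", delivered by a trained psychologist over 6 weeks. Under Recruitment, a psycho-oncologist contacts IG relatives after T0, "whereas CG will not be actively contacted". Under Control group (CG), counseling is open to CG relatives who seek it. The same section says that patients in both arms may ask for support but are not proactively offered a specific intervention.

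**Questionnaires.** Relatives and patients in both arms complete the PHQ-9 at T0 and T1. The Depression section describes it as nine DSM-derived items summed to 0–27. For the primary and secondary outcomes, "differences between the IG and CG at T1 will be assessed using aggregated questionnaire scores (mean values". Under Data collection, "The follow-up questionnaires (T1) will be sent by mail with a prepaid envelope for return". Researchers check the responses to promote complete follow-up, and the member responsible for assignment and data collection holds the code list. Under Blinding, "psycho-oncologists are not involved in recruitment and data collection".

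**The concern.** The SAE rule covers everyone, but the contact schedule reaches only one of the four groups (relatives and patients, each in two arms). Suicidality is usually found by asking or by disclosure in conversation. IG relatives have repeated, scheduled conversations with a psychologist; the other three groups have none. The discontinuation route adds to the imbalance, because CG participants have no study intervention to discontinue.

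Two things are at stake. First, a reader of the results will set the SAE counts side by side. A higher count in the IG could be read as harm from CALM when it reflects closer observation, and a low count in the CG or among patients could reassure falsely. Second, the rule asks for immediate reporting, but outside the IG sessions the article gives no stated step that would start a report.

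A related gap is that the definition does not separate suicidality already present at T0, which is completed before randomisation, from suicidality that is new at T1.

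**Working it through.** **1. Denominator.** Sample size calculation states 100 relatives per group for d = 0.4, alpha 0.05 and beta 0.2; the two-sided test is stated under Main research question. The normal approximation gives 99 per group (198 in total). The t-test version gives 99.08, rounded up to 100 per group (200 in total). The stated figure reproduces and is not in dispute. It serves here only as n = 100 per arm.

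**2. Scheduled routes, group by group.**

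| Group | Scheduled clinician contact | Discontinuation route | PHQ-9 at T0 and T1 |
|---|---|---|---|
| IG relatives | 3 × 45 = 135 min to 6 × 45 = 270 min | yes | yes |
| CG relatives | none; on own initiative only | in practice no | yes |
| IG patients | none; on request only | in practice no | yes |
| CG patients | none; on request only | in practice no | yes |

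The arm imbalance concerns relatives. For patients the arms are alike, and the gap is the lack of a stated route in either.

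**3. Effect of unequal detection.** Let p be the true proportion with suicidality and s the probability that a case is detected.

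Expected reported cases in an arm = n × p × s.

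With the same p in both arms, the expected reported IG:CG ratio = s(IG) / s(CG), whatever p is.

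The documents give neither p nor s, so every value below is an assumption.

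| s(IG) / s(CG) | Ratio | p = 2% | p = 5% | p = 10% |
|---|---|---|---|---|
| 0.9 / 0.2 | 4.5 | 1.8 vs 0.4 | 4.5 vs 1.0 | 9 vs 2 |
| 0.8 / 0.4 | 2.0 | 1.6 vs 0.8 | 4.0 vs 2.0 | 8 vs 4 |
| 0.6 / 0.4 | 1.5 | 1.2 vs 0.8 | 3.0 vs 2.0 | 6 vs 4 |
| 0.8 / 0.8 | 1.0 | 1.6 vs 1.6 | 4.0 vs 4.0 | 8 vs 8 |

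Example: 100 × 0.05 × 0.8 = 4.0 and 100 × 0.05 × 0.4 = 2.0.

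**4. Can the sign reverse?** Suppose CALM halved the true proportion (2.5% against 5%) and detection were 0.8 against 0.2. Reported cases would be 100 × 0.025 × 0.8 = 2.0 in the IG and 100 × 0.05 × 0.2 = 1.0 in the CG. A true benefit would appear as an excess.

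**5. What a common source would involve.** 200 dyads × 2 members × 2 time points = at most 800 PHQ-9 forms, all already planned.

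**The case against.** The strongest reply is that this is operational detail. The harms section states nothing false, and how SAEs are elicited may stand in the full protocol (version 3.1 according to Trial status), which is not shown. More clinician contact in a counseling arm is inherent in the design. This stands in part: silence on elicitation alone would be no finding. What remains is that the unequal contact is stated in the text, alongside an SAE rule that covers all participants.

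Four stronger readings are tempting, and the documents do not support them.

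- *The SAE comparison is biased and its result is predictable.* No between-arm SAE test is planned. CG relatives can ask for counseling, so their detection is lower and self-selected rather than zero. The size of any distortion cannot be computed.
- *The PHQ-9 is used only as a score, and nobody looks at the answers.* The sentence on aggregated scores governs the primary and secondary outcomes and does not exclude other uses. Researchers do check responses in both arms, although the stated purpose is complete follow-up.
- *Pseudonyms prevent identification.* The code list is held by the member responsible for data collection, so a respondent can be identified.
- *A positive answer on a mailed form is an unreported SAE.* The article mentions no self-harm item and does not equate a questionnaire answer with suicidality. Any count of such forms would rest wholly on assumed rates.

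A questionnaire check also has limits. The PHQ-9 looks back 2 weeks and T1 falls at about 6 weeks, so roughly the first 6 − 2 = 4 weeks are not covered. It cannot capture completed suicide, and it depends on the form being returned.

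**Conclusion.** The point holds in limited form and is a should-fix. As written, the trial's only SAE has a scheduled route to detection for IG relatives and for no one else, so counts for relatives cannot be compared between arms without confounding by surveillance. The direction rests on one premise: scheduled sessions with a psychologist find more cases than contact that the relative must seek. The ratio of 1.5 to 4.5 under no true difference illustrates assumed detection probabilities and is not an estimate for this trial.

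A reader might infer that this must be fixed before the trial can be relied on. The documents do not support that: no primary or secondary outcome, sample size or planned analysis is affected, and SAE counts are likely to be small. The point is closed if the full protocol already contains an equal check in both arms.

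**What to change.** Reconcile Intervention group (IG), Control group (CG), Recruitment, Blinding, Data collection and Monitoring: harms by stating one ascertainment procedure for suicidality, applied identically in both arms, to relatives and patients, at T0 and T1. The means are already in the plan: the PHQ-9 (assuming that it has a self-harm item) and the response check under Data collection, feeding the existing report to the principal investigator. Which answer counts as an SAE, and what care follows, are for the investigator to set.

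Report SAEs:

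- by randomised arm, separately for relatives and patients;
- by whether suicidality was present at T0 or new afterwards;
- by route of detection (questionnaire, counseling session, other).

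Show session-detected events in full and flag them as not comparable between arms. Leaving them out of safety reporting could hide real harm from the intervention. State the limits of the questionnaire route, including its 2-week window.

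The cost is a short amendment, one added purpose for a check that is already made on returned forms, more SAE reports and one extra table. No new visit or instrument is needed. If the full protocol already has such a check, citing it in the article is enough.
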